## 6.10 Training

Roche Diagnostics will be responsible for the training of practice staff in the use of the device and ongoing quality requirements (e.g. monthly control tests). A quality assurance programme will be run alongside the training and will include some parallel testing of training samples to ensure that staff who are being trained are achieving optimum results on the cobas 101 when compared with conventional laboratory testing

## 6.11 Practice follow-up

Each of the ten practices allocated to the POC group will undergo a training session in the use of the Cobas b 101 device. About half way through the study e.g. at 3 months, and at the end of the study practices will be contacted by PHO facilitators to document any additional staff time and/or other resources required by the use of the Cobas b 101 device and to assess its overall acceptability, feasibility and practice impact. The study will be continued until at least 1000 risk assessment have been performed and all the point of care consumables have been utilised by the POC group. It is estimated therefore the study duration will be in the order of 3-6 months.

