## **Study period**

Expected duration 3-6 months (dependent on practices' rate of risk assessment).

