## 5. Study Objectives

Primary study objective:

To evaluate the impact of POC testing for lipids (TC/HDL) and diabetes (HbA1c) on the frequency of completed CVD risk assessments in the eligible population. The primary aim of this study is to determine whether POC testing for lipids (TC/HDL) and diabetes (HbA1c) is at least as effective as the control (laboratory) on the frequency of completed cardiovascular disease (CVD) risk assessments in the eligible population at 12 months in primary care practice.

Secondary study objective(s):

1. To evaluate the impact of POC testing for TC/HDL and HbA1c on the frequency of incomplete ("parked") CVD risk assessments in the eligible population.
2. To evaluate the impact of POC testing for TC/HDL and HbA1c on CVD risk assessments in the eligible population by age, sex, deprivation quintile, for Māori and non Māori, diabetes, smoking status, and previous CVD risk score.
3. To evaluate the impact of POC testing for TC/HDL and HbA1c on the average duration of CVD risk assessment.
4. To evaluate whether the impact of POC testing is the same in urban areas (e.g. Whangarei City) as in rural areas and in large and small GP practices.
5. To conduct a cost analysis of POC testing compared with laboratory testing.
6. To evaluate the acceptability, feasibility and practice impact of POC testing for TC/HDL and HbA1c in general practice.

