**Table 1: Details of follow-up**

| Timing                          | Week 0                 | Week 0  | End of study  | End of study |
|---------------------------------|------------------------|---------|---------------|--------------|
| Description                     | Practice randomisation | PREDICT | Practice F/U  | PREDICT      |
| Form                            |                        |         | Questionnaire |              |
| Randomisation                   | X                      |         |               |              |
| Study eligible population       |                        | X       |               |              |
| Useability questionnaire        |                        |         | X             |              |
| CVD risk assessments            |                        |         |               | X            |
| Laboratory and Cobas b 101 data |                        |         |               | X            |

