Our updated sample size calculations are based on analyses estimating the number of eligible people who are eligible for first risk assessment and those that will require a follow-up CVD risk assessment (for example those over 15% CVD risk, and people with diabetes are recommended for annual screening). Within a 12 month period (Aug 2012-2013) it appeared that about 30% of the eligible population had a CVD risk assessment. We assume a primary event rate of 30% in the laboratory group and a 10% increase to 40% in the POC group. This figure is based on a study set in community pharmacies where POC testing for cholesterol risk management led to a 10% increase. The non-inferiority margin is set at 5%. Taking into account an intraclass correlation coefficient of 0.025 as suggested by Elley et al (2005) from three New Zealand CRCTs; a 0.025 one-sided level of significance and study power of 90%, we estimate a minimum sample size of 940 risk assessments (470 in each group) and 10 practices per group is needed assuming an average of 50 patients per practice. Therefore, the sample size is similar to the previous power calculations.

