**Table 4 Study Cobas b 101 supplies**

| Material name
(Product name)       | Material Number | Unit       | Quantity |
|---------------------------------------|-----------------|------------|----------|
| Cobas b101                            | 06378668190     | each       | 10       |
| HbA1c disc                            | 06378676190     | Box of 10  | 198      |
| HbA1c control                         | 06380204190     | 2 vials    | 120      |
| Lipid panel disc                      | 06380115190     | Box of 10  | 198      |
| Lipid panel control                   | 06380182190     | 2 vials    | 120      |
| 5 x Safe-T-Pro Plus
Lancing device | 03603539200     | Box of 200 | 5        |

Roche Diagnostics NZ Ltd will supply additional consumables for the training sessions for the POC group and laboratory groups.

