### Key milestones

| Date           | Milestone                                                                                   |
|----------------|---------------------------------------------------------------------------------------------|
| May 2013       | Ethics submitted                                                                            |
| June 2013      | Ethics approval                                                                             |
| July 2013      | Recruit practices                                                                           |
| August 2013    | Start of study                                                                              |
| August 2013    | Study halted due to manufacturing problems cobas b 1010 discs                               |
| May 2014       | Study recommenced after re-validation cobas discs, retraining practices and Ethics approval |
| June 2015      | Estimated end of study                                                                      |
| September 2015 | Analysis complete.                                                                          |
| November 2015  | Paper submitted.                                                                            |

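### The primary-outcome window is fixed in incompatible ways (12 months, end of study, 3-6 months, until supplies are used) with no opening date, while the sample size holds for 12 months only

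*Protocol*

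**What the plan says.** The current protocol text sets the time frame of the primary outcome in several places:

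- **Aim** (section 1, Objectives; section 5): "completed cardiovascular disease (CVD) risk assessments in the eligible population at 12 months in primary care practice".
- **Outcome measure** (section 1, Criteria for evaluation; section 6.8): a completed assessment at the end of the study, with no month given. Section 7.1 words it as completion during the study.
- **Duration** (section 1, Study period): "Expected duration 3-6 months". Section 6.11 repeats this estimate.
- **End rule** (section 6.11): the study is to be "continued until at least 1000 risk assessment have been performed and all the point of care consumables have been utilised by the POC group".
- **Calendar** (Appendix 5, Key milestones): start in August 2013; in the same month, "Study halted due to manufacturing problems cobas b 1010 discs"; restart in May 2014; estimated end in June 2015. As extracted, the follow-up row of the timeline covers Q4 2013 to Q1 2015.
- **Week 0** (Table 1, Details of follow-up): practice randomisation and the eligible population both sit here. No calendar date is attached.

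The planning figures are in section 7.1: "Within a 12 month period (Aug 2012-2013) it appeared that about 30% of the eligible population had a CVD risk assessment". The same paragraph assumes 30% against 40%, a margin of 5 points and 940 in total. Section 7.2.2 tests against -5% without naming a period.

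**The concern.** Completion is cumulative: the longer the window, the larger the proportion in both arms. A fixed absolute margin therefore has no stable meaning until the window is fixed. Five points is a modest concession against a 30% control rate and a large one against half that rate. Power moves with the window too.

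Because the outcome is read at the end of the study, whatever ends the study also sets the window. Here that is partly the use of supplies in the POC arm of an open trial, so the date of the primary assessment depends on uptake of the intervention under test. The opening of the window is equally open. Nothing says whether Week 0 is August 2013 or May 2014, and about nine months of halt lie between them.

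**Working it through.** **1. The plan's own figure.** Inputs from section 7.1: 30% laboratory, 40% POC, margin 0.05, one-sided alpha 0.025, power 90%, ICC 0.025, 50 per practice. The 470 per arm is treated as the denominator of the proportion, as the formula requires.

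- Individual n per arm = (1.960 + 1.282)² × (0.30×0.70 + 0.40×0.60) / (0.10 + 0.05)² = 10.51 × 0.45 / 0.0225, rounded up to 211.
- Design effect = 1 + 49 × 0.025 = 2.225.
- 211 × 2.225 = 469.5, so 470 per arm and 940 in total. This matches the protocol.
- Power at 470: SE = √(0.45 × 2.225/470) = 0.0462; 0.15/0.0462 − 1.96 = 1.29, giving 90.1%.

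The calculation is sound for a 12-month window.

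**2. The same margin in other windows.** The protocol does not say how completions accrue, so two assumptions are shown: linear, p × months/12; and constant hazard, 1 − (1 − p)^(months/12).

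| Window | Accrual | Laboratory | POC | 5 points / laboratory rate | Power at 470 per arm |
|---|---|---|---|---|---|
| 12 months | as planned | 30.0% | 40.0% | 17% | 90.1% |
| 6 months | linear | 15.0% | 20.0% | 33% | 77.4% |
| 6 months | constant hazard | 16.3% | 22.5% | 31% | 83.1% |
| 13 months (May 2014 to June 2015) | both | 32-32.5% | 42.5-43.3% | 15-16% | 91-92% |
| 22 months (August 2013 to June 2015) | both | 48-55% | 61-73% | 9-10% | 96-99.9% |

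Example, 6 months linear: SE = √((0.15×0.85 + 0.20×0.80) × 2.225/470) = 0.0369; (0.05 + 0.05)/0.0369 − 1.96 = 0.75, giving 77.4%. For 90% power at 6 months, 581-675 per arm would be needed.

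**3. The end rule against its own estimate.** Table 4 in section 10.1 lists 198 boxes of 10, so 1,980 discs of each type.

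- When 1,000 assessments are reached, the POC arm has done about 500 on an equal split, or 1,000 × 40/70 = 571 on the planned rates.
- With one disc of each type per POC assessment, supplies last 1,980/571 = 3.5 to 1,980/500 = 4.0 times as long as it takes to reach 1,000.
- If 1,000 takes 3 months, supplies last about 10-12 months. If it takes 6, they last about 21-24 months.
- Control testing shortens this somewhat. Assuming two control discs of each type per practice per month for 13 months, 10 × 2 × 13 = 260 are used. The remaining 1,720 still give 1,720/571 = 3.0 to 1,720/500 = 3.4 times.

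On the protocol's own quantities the consumables condition is the binding one, and it does not yield 3-6 months.

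**The case against.** The best defence is that the 12-month reading is already dominant. Section 7.1 ties the 30% to 12 months, the aim says the same, and restart to estimated end is about 13 months, where power is 91-92%. The 3-6 months is labelled as expected or estimated and is not an outcome definition. By the date of this version (30 March 2015, Appendix 6) a stop at 3 or 6 months after restart could no longer happen. All of this stands. It means the 6-month row shows how much depends on the window, not what is likely to occur. It does not supply an opening date or a period for the margin, and it does not remove the end-of-study definition.

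A reader might infer three stronger things that the documents do not support:

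- **That the 30% rate belongs to no period.** It is explicitly a 12-month rate. What is missing is a trial window tied to it.
- **That the end rule pushes systematically towards a false claim of non-inferiority.** The rule requires both conditions. Slow POC uptake makes supplies last longer, lengthens the study, raises the cumulative rates and makes five points relatively stricter (9-10% of the control rate at 22 months). A shorter window also costs power.
- **That counting the halt would bring a clearly inferior result inside the margin.** No text says the halt months count. If they did, and both arms used laboratory testing then, nine shared months under constant hazard would multiply the difference by 0.7^(9/12) = 0.765. A deficit of 8 points, taken as an illustration, becomes 6.1 and stays outside the margin. Under linear accrual it does not change.

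**Conclusion.** The concern holds as an inconsistency in how the primary outcome is fixed. The aim, outcome measure, duration, end rule and calendar cannot all be followed, and no opening date is given, so two analysts could compute different primary results from the same data. This goes beyond detail that could wait for an analysis plan, because the protocol itself states incompatible windows.

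The sample size is correct for 12 months. In a 6-month window the margin would nearly double in relative terms, from 17% to 31-33% of the control rate, and power would fall from 90.1% to about 77-83%. Those figures rest on the assumed accrual patterns. The conflict between the end rule and the 3-6 month estimate rests on the Table 4 quantities and on one disc of each type per POC assessment. No direction of bias is established.

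**What to change.** - Define the primary outcome as a completed assessment, yes or no, within one fixed window, with the same calendar dates in both arms and a stated opening date.
- Fix the eligible list at that opening date and count only assessments completed within the window.
- Twelve months from the May 2014 restart matches the aim, the source of the 30% and the follow-up planned to June 2015. If another window is chosen, the control rate, margin and sample size need to be re-derived for it.
- State in sections 7.1 and 7.2.2 that the -5 point margin applies to the 12-month proportion.
- Stop using the assessments-and-consumables rule and the 3-6 month text to set the primary outcome date. Align sections 1, 5, 6.8, 6.11 and 7.1, Table 1 (Details of follow-up) and Appendix 5.

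The cost is mainly amendment wording. Section 6 says PREDICT captures assessments automatically before, during and after the study, and follow-up to June 2015 is already planned. If the eligible list was drawn in 2013, it would have to be drawn again as at the restart date. No interim analysis is planned and the analysis is to be blinded to allocation, so the window can be fixed without knowledge of results by arm.

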## 6.12 Detail of data collection

### 6.12.1 Eligibility, randomisation and baseline assessment

All practices in Manaia and Te Tai Tokerau PHOs will be eligible to be included in the study. The first twenty to provide informed consent will be randomised. A de-identified list of eligible patients in the participating practices will be generated using the Northland PHOs' population register provided by PREDICT.

### 6.12.2 CVD risk assessment data collection

CVD risk assessment data will be collected by the PREDICT software. At the end of the study the investigators will receive de-identified PREDICT data by practice on the study population who have had a completed or parked CVD risk assessment. The PREDICT data will be provided to the investigators by practice separated into two groups. At the end of the analysis the allocation assignment to POC or laboratory group will be revealed to the investigators.

### 6.12.3 *Qualitative assessment of practice acceptability*

The qualitative assessment (practice questionnaire) will collect information from practices allocated to the POC group on where the POC testing was done, who did it, how user friendly was the tool, how user friendly was the integration with the PREDICT CVD risk assessment, what extra time and resources were required, what changes in work flow were required, any teething difficulties or issues arising during the time period, and potential opportunity costs imposed by having the Cobas b 101 device in the practice.

A short questionnaire will also be administered to the control practices asking about current practice for obtaining HbA1c and TC/HDL blood results, the major barriers to CVD risk assessment in their practice and their perceptions about the acceptability and feasibility of having the cobas b 101 device in the practice.

**Table 1: Details of follow-up**

| Timing                          | Week 0                 | Week 0  | End of study  | End of study |
|---------------------------------|------------------------|---------|---------------|--------------|
| Description                     | Practice randomisation | PREDICT | Practice F/U  | PREDICT      |
| Form                            |                        |         | Questionnaire |              |
| Randomisation                   | X                      |         |               |              |
| Study eligible population       |                        | X       |               |              |
| Useability questionnaire        |                        |         | X             |              |
| CVD risk assessments            |                        |         |               | X            |
| Laboratory and Cobas b 101 data |                        |         |               | X            |

## 7. Statistical Considerations

### 7.1 Sample size

The study will involve a two-arm parallel cluster randomised controlled trial (CRCT) design with 20 practices (10 practices per arm). The primary outcome is whether the eligible patients have had a completed CVD risk assessment during the study. Preliminary analyses indicated that at least 70% of the enrolled populations within Manaia and Te Tai Tokerau PHOs have had a completed CVD risk assessment since 2006. Many of these people will be due for repeat CVD risk assessment. Significant delays to the conduct of this trial have occurred both prior to commencement and having to halt the trial due to manufacturing problems of the HbA1c discs. During this time practices have accelerated their CVD risk assessments in order to meet the national target (by July 2014 that 90% of the eligible population have had a CVD risk assessment in the previous 5 years.) As at April 2014, the two PHOs have screened approximately 80% of their eligible enrolled populations over the last five years. Therefore this trial now needs to adopt **a priori a non-inferiority hypothesis**.

Our previous sample size calculations May 2013, were as follows; We assumed a primary event rate of 70% in the laboratory group and a 10-15% increase to 85% in the POC group. This figure is based on a study set in community pharmacies where POC testing for cholesterol risk management led to a 10% increase. Taking into account an intraclass correlation coefficient of 0.025 as suggested by Elley et al (2005) from three New Zealand CRCTs; a 5% two-sided level of significant test and study power of 90%, we estimate a minimum sample size of 1000 risk assessments is needed (on average 50 patients per practice).

Our updated sample size calculations are based on analyses estimating the number of eligible people who are eligible for first risk assessment and those that will require a follow-up CVD risk assessment (for example those over 15% CVD risk, and people with diabetes are recommended for annual screening). Within a 12 month period (Aug 2012-2013) it appeared that about 30% of the eligible population had a CVD risk assessment. We assume a primary event rate of 30% in the laboratory group and a 10% increase to 40% in the POC group. This figure is based on a study set in community pharmacies where POC testing for cholesterol risk management led to a 10% increase. The non-inferiority margin is set at 5%. Taking into account an intraclass correlation coefficient of 0.025 as suggested by Elley et al (2005) from three New Zealand CRCTs; a 0.025 one-sided level of significance and study power of 90%, we estimate a minimum sample size of 940 risk assessments (470 in each group) and 10 practices per group is needed assuming an average of 50 patients per practice. Therefore, the sample size is similar to the previous power calculations.

### 7.2 Statistical analyses

This study has been designed with the assistance of statisticians at the NIHI. These statisticians will also advise and assist with the analysis of the study results. Individual patient's data entered into the PREDICT decision support programme will be imported into an Oracle database at the NIHI using the encrypted NHI, and then extracted into SAS (version 9.3) for analysis. Data analyses will be carried out on an intention-to-treat basis, and will be specified a priori a statistical analysis plan prepared by the study statistician (and agreed upon by all members of the Advisory Group). No interim analyses will be undertaken. All statistical tests will be two-sided with 5% level of significance.

### 7.2.1 *Baseline characteristics*

The following baseline characteristics will be collected: age group, gender, deprivation index quintile, Māori/non Māori ethnicity, previous CVD risk score, and past history of CVD based on previous risk assessment data. Baseline characteristics will be summarised using descriptive statistics. Continuous variables will be described as numbers of observed and missing values, mean, standard deviation, median, minimum and maximum. Categorical variables will be described as frequencies and percentages.

### 7.2.2 *Study effects*

Generalized estimating equations (GEE) or random effects mixed models will be used in treatment evaluations, adjusting for the effect of clustering within practices and important baseline prognostic factors (e.g. practice location (urban/rural), size (number of GPs). Analysis of the non-inferiority hypothesis for the primary outcome will be evaluated by observing whether the lower limit of a one-sided 97.5% CI (or equivalently a two-sided 95% CI) is above the non-inferiority limit of -5%. In the case that non-inferiority is evident, assessment as to whether POC is superior to the control will be carried out using the same approach but comparing to a zero difference. A per-protocol analysis will also be performed in order to check the robustness of the results. Time series analysis will be conducted to describe changes in patterns of use of the POC device, for example increased use initially followed by a decline to a steady state level. Sensitivity analyses for the rate of CVD risk assessment will then be calculated for the latter period as being more indicative of ongoing community use of the POC device.

Duration of CVD risk assessment will be calculated from the start of the population of the PREDICT CVD risk assessment template to completion, i.e. when the five year CVD risk value is calculated.

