## 6. Study Design

This is a pragmatic, prospective, open, blinded endpoint, cluster randomised controlled non-inferiority trial in primary care.

The study setting is the patients enrolled in GP practices within the Northland region of New Zealand that belong to either Manaia Health Primary Healthcare Organization (PHO) or Te Tai Tokerau PHO. Manaia Health has 24 practices and Te Tai Tokerau has 15. A cluster randomised controlled trial is proposed within twenty of these general practices who use PREDICT and agree to participate in the study.

The eligible population is comprised of patients enrolled in these practices who are aged between 35-79 years, who as determined by their GP, meet age, sex and ethnicity guideline criteria for CVD risk assessment (Table1) and do not have a previous recorded CVD risk assessment or if they have had a previous CVD risk assessment are overdue for their next check (Table 2). All CVD risk assessment data will be automatically captured within the PREDICT server before, during, and after the study as part of usual clinical practice.

The unit of randomisation will be the practice and data collection will be at the individual patient level. The study involves random allocation of the practices to either the POC group (Cobas b 101) or laboratory (control) group. A cluster RCT design was necessary because the cobas b 101 device will be provided to the practice as a cluster level intervention.

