### 6.5 Randomisation

Participating practices will be randomised by the biostatistician into POC and laboratory groups. Randomisation will be stratified by practice size (number of effective FTE GPs where 0.8 FTE = 1.0 effective FTE: <2 effective FTE small, ≥2 effective FTE large)) and rurality of location (urban [within the Whangarei city boundary] or rural). As these factors are potentially associated, directly or indirectly, with the probability of CVD risk assessment completion; stratification will ensure a balance in these potential confounders between the two study arms.

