### 7.2.3 *Run charts*

Run charts (or statistical process control [SPC] charts) will be developed to assess the impact of the potential novelty imposed by having the POC testing device, any teething difficulties, changes in work process and the Hawthorne effect from being in a study by tracking risk assessment behaviour in the practices. At the end of the study run charts of monthly CVD risk assessments counts for all of the practices will be generated for the duration of the study and for the 12 months prior. Special cause variation (statistically significant shifts in practice) occurring during that time and their association with PHO or the study will be determined using the standard Shewhart criteria.

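### The primary model does not name each practice's pre-study assessment activity as a covariate, and its size variable is not the one used to stratify randomisation, so some precision is probably given up.

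*Protocol*

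**What the plan says.** **Model.** Protocol 7.2.2 (Study effects) specifies GEE or random effects mixed models that allow for clustering within practices and adjust for "important baseline prognostic factors (e.g. practice location (urban/rural), size (number of GPs". The two factors are introduced as examples. Section 7.2 leaves the detailed analysis to a statistical analysis plan, which is not at hand.

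**Baseline list.** Section 7.2.1 lists patient-level characteristics only. No practice-level measure of past assessment activity appears.

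**Pre-study data.** Section 6 states: "All CVD risk assessment data will be automatically captured within the PREDICT server before, during, and after the study". Section 7.2.3 commits to run charts in which "monthly CVD risk assessments counts for all of the practices will be generated for the duration of the study and for the 12 months prior". Those counts have no other stated use.

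**Stratification.** Section 6.5 says: "Randomisation will be stratified by practice size (number of effective FTE GPs where 0.8 FTE = 1.0 effective FTE", with small meaning below 2 effective FTE and large meaning 2 or more. The other stratum is urban or rural location.

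**Design figures.** Section 7.1 describes a "cluster randomised controlled trial (CRCT) design with 20 practices (10 practices per arm" and states: "We assume a primary event rate of 30% in the laboratory group and a 10% increase to 40% in the POC group". It adds "The non-inferiority margin is set at 5" percent and "Taking into account an intraclass correlation coefficient of 0.025", with one-sided 0.025, 90% power and an average of 50 patients per practice. The result is 470 per group, 940 in all.

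**Dates.** The key milestones in Appendix 5 put practice recruitment in July 2013, start and halt in August 2013, and the restart in May 2014. The follow-up table in 6.12.3 puts randomisation at week 0. No second randomisation is described.

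**The concern.** With 10 practices per arm, much of the uncertainty comes from differences between practices. How actively a practice assessed patients in the year before allocation is a natural predictor of how actively it does so during the study. Section 6.5 stratifies on size and location because they may be associated with completion; past activity is a more direct measure of the same thing. Leaving it unnamed risks a wider interval than the data could support, in a trial judged by an interval against a 5-point margin.

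Two points in the text add to this and need no assumption about correlation:

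- Number of GPs and effective FTE are different variables, so a model fitted as worded need not adjust for the stratum used in randomisation.
- The 12-month run-chart window has no fixed anchor. If it is counted back from the May 2014 restart, most of it falls after allocation and cannot serve as a baseline.

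**Working it through.** **Inputs.** From 7.1: 10 practices per arm, 50 patients each, ICC 0.025, 30% versus 40%, margin 5 points, one-sided 0.025, power 90%. Not in the documents: r, the correlation between a practice's true pre-study and in-study rates after the other covariates. I assume 0.5 to 0.8 and show 0.3 as a low case.

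**1. The protocol's own figure.**
- Per arm without clustering: (1.960 + 1.282)² × (0.30×0.70 + 0.40×0.60) / (0.10 + 0.05)² = 10.507 × 0.45 / 0.0225 = 210.1, so 211.
- Design effect: 1 + 49 × 0.025 = 2.225.
- 211 × 2.225 = 469.5, so 470 per group and 940 in total. The figure reproduces, with no covariate gain built in.

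**2. Between-practice spread at 30%.**
- Between-practice variance: 0.025 × 0.21 = 0.00525, an SD of 7.2 points.
- Within-practice part of a practice mean: 0.21 × 0.975 / 50 = 0.004095.
- Chance difference between arms in mean true practice rate: SD 7.2 × √(2/10) = 3.2 points.

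**3. Standard error with the baseline covariate.** SE = √{2 × [0.00525 × (1 − r²) + 0.004095] / 10}.

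| r | SE | Reduction |
|---|---|---|
| none | 0.0432 | – |
| 0.3 | 0.0421 | 2.6% |
| 0.5 | 0.0401 | 7.3% |
| 0.8 | 0.0346 | 20.0% |

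**4. Allowing for error in the observed baseline rate.** If that rate rests on 50 patients, its reliability is 0.00525 / (0.00525 + 0.004095) = 0.56, and r² is replaced by 0.56 × r². The reduction becomes 1.4% at r = 0.3, 4.0% at 0.5 and 10.7% at 0.8.

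**5. Non-inferiority power.** The variance factor is F = 0.975 + 1.25 × (1 − r²), and SE = √{[p₁(1 − p₁) + p₂(1 − p₂)] × F / 500}. Power uses the noncentral t, with 16 df (20 practices less intercept, arm, location and size; critical value 2.120) or 15 df once the baseline is added (2.131). Baseline rate taken as measured without error:

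| r | F | Power, 30% vs 40% | Power, 30% vs 30% |
|---|---|---|---|
| none | 2.225 | 88% | 19% |
| 0.3 | 2.11 | 90% | 20% |
| 0.5 | 1.91 | 92% | 21% |
| 0.8 | 1.43 | 97% | 27% |

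With baseline reliability 0.56, power at 30% versus 40% is about 90% (r = 0.5) to 94% (r = 0.8). Below about r = 0.14 the lost degree of freedom cancels the gain in interval width.

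**6. The size variable.** Three GPs at 0.5 FTE give 1.5 / 0.8 = 1.875 effective FTE, a small practice. Two GPs at 0.8 FTE give 2.0 effective FTE, a large one. Number of GPs can therefore rank practices opposite to the stratum.

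**7. The window.** Twelve months back from May 2014 is May 2013 to April 2014. If allocation was in August 2013, about 9 of those 12 months (August 2013 to April 2014) fall after it.

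**The case against.** The case on the other side limits this point in several ways, and most of it stands.

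- A reader might infer that the protocol excludes the covariate. It does not. The list is open, and a final covariate list commonly belongs in the unseen statistical analysis plan. The covariate is unnamed, not ruled out.
- A reader might infer that a completion rate is already being extracted. Section 7.2.3 plans counts. The only eligible list described (6.12.1, and week 0 in the follow-up table) is the study population's. The figure of about 30% for August 2012 to 2013 in 7.1 suggests that a rate can be derived, but it is pooled over practices.
- A reader might infer bias from chance imbalance. The clustered interval already carries between-practice variation, and so does the design effect. Without the covariate the analysis remains valid.
- A reader might infer that the planned power depends on the adjustment. The 470 per group reproduces without it.
- The correlation is not in the documents, and there are reasons it could be modest. Section 7.1 says practices accelerated towards the national target, Table 2 removes recently assessed low-risk patients from the eligible pool for years, and the proposed window ends about ten months before the restart.
- Larger practice samples would make the gain larger, but 50 on average is the only cluster size that the documents give.

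What remains is that the activity data are held and used only descriptively, that naming this covariate in advance is a near-free improvement, and that the size variable does not match 6.5.

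**Conclusion.** The point holds as one of precision and wording. Section 7.2.2 names neither the practice's pre-study activity nor the size stratum as randomised. At ICC 0.025 and 50 patients per practice, the standard error would fall by about 7% to 20% if r is 0.5 to 0.8, by about 4% to 11% if the baseline rate is itself measured on 50 patients, and negligibly at r of 0.3 or below. Under 30% versus 40%, power moves from about 88% to at most 92% to 97%. With equal arms it stays low, at 19% rising to no more than 27%, so the adjustment does not rescue that scenario.

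Confidence is high on what the text says and moderate on the size, which rests on an assumed correlation and does not separate out what location and size already explain. The 9-month figure assumes allocation in August 2013 and no re-randomisation.

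**What to change.** In 7.2.2, and in the statistical analysis plan, name these covariates for the primary model:

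1. The two strata as randomised: effective FTE below 2 versus 2 or more, and urban versus rural.
2. The practice's 12-month assessment activity before allocation: completed assessments divided by eligible patients, or by the register list if no historic eligible denominator exists.

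State that the window ends before the 2013 allocation (about August 2012 to July 2013) and is not counted back from the May 2014 restart. Fix the denominator in advance.

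The cost is one degree of freedom out of about 16, and a practice-level PREDICT extract for a window that may differ from the run-chart window. No extra recruitment is needed.
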